## Abstract

**Background::**

There are limited studies on the effects of statins on outcomes in the
moderate chronic kidney disease (CKD) population and their trajectory to
end-stage kidney disease.

**Objective::**

To examine the long-term effects of lipid-lowering therapy on all-cause
mortality, cardiovascular morbidity, CKD progression, and socioeconomic
well-being in Australian, New Zealand, and Malaysian SHARP (Study of Heart
and Renal Protection) trial participants—a randomized controlled trial of a
combination of simvastatin and ezetimibe, compared with placebo, for the
reduction of cardiovascular events in moderate to severe CKD.

**Design::**

Protocol for an extended prospective observational follow-up.

**Setting::**

Australian, New Zealand, and Malaysian participating centers in patients with
advanced CKD.

**Patients::**

All SHARP trial participants alive at the final study visit.

**Measurements::**

Primary outcomes were measured by participant self-report and verified by
hospital administrative data. In addition, secondary outcomes were measured
using a validated study questionnaire of health-related quality of life, a
56-item economic survey.

**Methods::**

Participants were followed up with alternating face-to-face visits and
telephone calls on a 6-monthly basis until 5 years following their final
SHARP Study visit. In addition, there were 6-monthly follow-up telephone
calls in between these visits. Data linkage to health registries in
Australia, New Zealand, and Malaysia was also performed.

**Results::**

The SHARP-Extended Review (SHARP-ER) cohort comprised 1136 SHARP participants
with a median of 4.6 years of follow-up. Compared with all SHARP
participants who originally participated in the Australian, New Zealand, and
Malaysian regions, the SHARP-ER participants were younger (57.2 [48.3-66.4]
vs 60.5 [50.3-70.7] years) with a lower proportion of men (61.5% vs 62.8%).
There were a lower proportion of participants with hypertension (83.7% vs
85.0%) and diabetes (20.0% vs 23.5%).

**Limitations::**

As a long-term follow-up study, the surviving cohort of SHARP-ER is a
selected group of the original study participants, which may limit the
generalizability of the findings.

**Conclusion::**

The SHARP-ER study will contribute important evidence on the long-term
outcomes of cholesterol-lowering therapy in patients with advanced CKD with
a total of 10 years of follow-up. Novel analyses of the socioeconomic impact
of CKD over time will guide resource allocation.

**Trial Registration::**

The SHARP trial was registered at ClinicalTrials.gov NCT00125593 and ISRCTN
54137607.

## What was known before

In people with moderate to severe kidney disease, over a median follow-up of 4.9
years, a combination of simvastatin and ezetimibe, compared with placebo, produced a
17% proportional reduction in major atherosclerotic events (nonfatal myocardial
infarction or coronary death, nonhemorrhagic stroke, or any arterial
revascularization procedure).

## What this adds

This study aims to extend the follow-up of these individuals to assess the long-term
outcomes of statin therapy as kidney disease declines. This study will also provide
novel understandings of the economic burden of chronic kidney disease for patients
and their families.

## Introduction

Chronic kidney disease (CKD) is a key element of the increasing global burden of
chronic diseases.^1^ The increasing prevalence of CKD has been well documented,^2,3^ as has its association with both
cardiovascular disease and premature death.^4^ Cardiovascular disease is the leading cause of death in people with CKD, and
its prevalence rises with declining kidney function. Importantly, individuals with
mild to moderate CKD are more likely to die from cardiovascular causes than develop
end-stage kidney disease, the final stage of CKD.^5^ Despite this, there are limited data from large-scale randomized trials on
treatments that can slow or halt kidney disease progression or prevent
cardiovascular events.

Several randomized placebo-controlled trials have tested the effects of lowering
low-density lipoprotein cholesterol (LDL cholesterol) with statin-based therapy in
patients with CKD.^6-9^ The Study of Heart and Renal
Protection (SHARP) is the largest such study, having randomized 9270 participants
with moderate to severe kidney disease in 18 countries. In SHARP, compared with
placebo, combination therapy with simvastatin 20 mg and ezetimibe 10 mg yielded an
average LDL cholesterol reduction of 0.85 mmol/L (SE = 0.02) over a median follow-up
of 4.9 years, producing a 17% proportional reduction in the key prespecified outcome
of major atherosclerotic events (MAE) (nonfatal myocardial infarction or coronary
death, nonhemorrhagic stroke, or any arterial revascularization procedure) (rate
ratio [RR] = 0.83; 95% confidence interval [CI] = 0.74-0.94; *P* = .0021).^9^

Long-term follow-up of efficacy and safety in randomized trials of statins in other
populations has demonstrated continuing benefits.^10-14^ However, there are currently
only limited examples of such extended follow-up in patients with CKD.^13,15,16^ Extended
follow-up of the SHARP cohort offers a unique and valuable resource to further
characterize the impact of LDL cholesterol lowering on cardiovascular events, as
well as explore the factors associated with CKD progression, and the long-term
safety of lipid lowering in those with CKD. To this end, the SHARP Post-Trial
Follow-Up (PTFU) study is being undertaken in many of the original countries that
participated in SHARP and will determine the long-term effects of 4.9 years of
median exposure to simvastatin plus ezetimibe or matching placebo among surviving
SHARP participants in relation to major atherosclerotic and major vascular events
(MVE); progression to end-stage renal disease (defined as the need for long-term
dialysis or renal transplantation) among patients not on maintenance dialysis at
randomization to simvastatin plus ezetimibe versus placebo in SHARP; and long-term
safety, through assessment of site-specific incident cancers (other than nonmelanoma
skin cancer) and mortality by cause.

The SHARP-Extended Review (SHARP-ER) study is part of this broader international
initiative and will additionally explore the social and economic impact of CKD on
individuals and their household. The SHARP-ER study methods will form the main focus
of this article.

## Methods

### Design

The SHARP-ER study is a longitudinal cohort study, extending the follow-up of
participants in participating centers in Australia, New Zealand, and Malaysia
who were alive at the end of the SHARP trial.

### SHARP Trial

Details of the recruitment of participants and the study design have been
published previously.^9,17^ In brief, 9270 participants aged 40 years or older with CKD
(defined as at least 1 measurement of serum creatinine of at least 150 μmol/L in
men or 130 μmol/L in women) with no known history of myocardial infarction and
coronary revascularization were enrolled between 2003 and 2006 in 18 countries.
Participants were randomized in the ratio of 4:4:1 to a combination of
simvastatin and ezetimibe, matching placebo, or simvastatin 20 mg alone (Figure A1). Those
allocated to simvastatin alone were re-randomized after 1 year to one of the
other 2 comparison arms. After initial randomization, participants were followed
up in study clinics at 2 and 6 months, and then every 6 months for at least 4
years. At each of these visits, information was recorded on all serious adverse
events. A double-dummy method ensured that participants and staff remained
unaware of treatment allocation. Although SHARP participants were given the
option to discover their treatment after the completion of the original SHARP
study, fewer than 3% of participants exercised this option in the global SHARP
cohort.

### SHARP Post-Trial Follow-Up

The SHARP-PTFU seeks to provide long-term follow-up of the global cohort of SHARP
participants alive at the end of the SHARP trial. It will assess the primary and
secondary outcomes of SHARP over an additional 5 years with participating
centers using a number of methods, including post-trial questionnaires and
linkage to routinely collected national data sets (eg, hospital admission data,
cancer and mortality data).

As a component of SHARP-PTFU, the SHARP-ER study will contribute primary and
secondary post-trial outcome data to the PTFU, with the differences in the 2
initiatives summarized in Table 1.

**Table 1. table1-2054358119879896:** Differences Between SHARP-ER Study and the Global SHARP-PTFU Study.

	SHARP-ER study	SHARP-PTFU study
Population	SHARP survivors in Australia, New Zealand, and Malaysia	All SHARP survivors
Outcome measures	Face-to-face visits Telephone interviews Study questionnaires Linkage to registry data	Linkage to registry data
Outcomes	Major atherosclerotic events^a^ Major vascular events^b^ Renal outcomes^c^ Socioeconomic outcomes^d^	Major atherosclerotic events Major vascular events Renal outcomes
Follow-up	5 years	5 years with ongoing linkages planned

*Note.* SHARP = Study of Heart and Renal Protection;
SHARP-ER = Study of Heart and Renal Protection-Extended Review; PTFU
= Post-Trial Follow-Up

a Major atherosclerotic events defined as coronary death, myocardial
infarction, nonhemorrhagic stroke, or any revascularization
procedure (excluding vascular access surgery for dialysis).

b Major vascular events defined as hemorrhagic stroke and noncoronary
death.

c Renal outcomes defined as initiation of long-term renal replacement
therapy or renal transplantation.

d Socioeconomic outcomes will include an assessment of (1)
illness-related catastrophic expenditure, (2) illness-related
poverty, and (3) economic hardship.

The SHARP-ER commenced recruitment in August 2012. All participants alive at the
final SHARP study visit in participating centers in Australia, New Zealand, and
Malaysia (August 2010) who were not previously documented as having withdrawn
consent were eligible for inclusion in SHARP-ER. Exclusion criteria for SHARP-ER
were the presence of concomitant major illness that would limit the
participant’s follow-up (in the opinion of the treating physician), a high
likelihood that the participant would not adhere to follow-up, and inability to
provide informed consent for reasons of mental or physical incapacity.

The study was conducted in accordance with the approved study protocol, the
principles of the “Declaration of Helsinki,” and the laws and regulations of the
relevant countries. All participating centers obtained independent ethics
approval prior to study commencement.

validated tools to evaluate health-related quality of life (HR-QoL)^18^ and the social,^19^ cognitive, and emotional impacts of kidney disease.^20^ The HR-QoL was measured through telephone interview by a central
interviewer (blinded to SHARP study allocation) at the initial visit, followed
by assessments at 3.5 and 5 years of follow-up. These interviews used the
EuroQOL 5 dimensions questionnaire (EQ-5D) and a Health Services Usage
Questionnaire. In addition, a 56-item detailed economic survey was used to
assess the socioeconomic impact of CKD. This included an assessment of (1)
out-of-pocket expenditure on illness not covered by insurance, such as
expenditure on health care, medications, investigations, and paid care; (2)
economic hardship, defined as an inability to make necessary household payments,
such as housing, energy, food, and health care costs, or requiring assistance to
meet such costs^21^; (3) household income in the past 12 months, measured against the median
income levels obtained from National Statistical Bureau.

Where available, data linkage using registries was used as secondary
ascertainment for mortality (using national death registries and Australian
Institute of Health and Welfare’s National Death Index^22^) and dialysis commencement (using renal replacement therapy [RRT]
registries: the Australian and New Zealand Dialysis and Transplant Registry
[ANZDATA; which captures 99% of all participants commencing RRT in Australia and
New Zealand]^23^ and the Malaysian National Renal Registry). In addition, consenting
participants were linked to the Medicare Benefits Schedule (MBS)^24^ and the Pharmaceutical Benefits Scheme (PBS)^25^ in Australia to evaluate the health care costs of CKD and long-term LDL
cholesterol–lowering treatment.

A limited assessment of the deceased participants who were alive at SHARP study
closure, but died prior to the SHARP-ER study, was also undertaken. This
included date and cause of death (from death certificates), and requirement for
dialysis in the period between the last assessment for the SHARP study and
death.

### Study Outcomes

The primary objective of the SHARP-ER study is to contribute to the description
of the long-term effects of SHARP study treatments, as part of the larger PTFU,
on MAE (coronary death, myocardial infarction, nonhemorrhagic stroke, or any
revascularization procedure [excluding vascular access surgery for dialysis])
and MVE (hemorrhagic stroke and noncoronary death). An important secondary
objective of the study is the long-term effects of the SHARP study treatment on
rates of CKD progression, defined by initiation of long-term RRT or renal
transplantation. Other secondary outcomes included cancer development (excluding
nonmelanoma skin cancer) and all-cause mortality. These outcomes will be
analyzed using an intention-to-treat analysis

The SHARP-ER study also measured the economic impact of CKD on participants and
households at visits 1 and 3. This included a detailed appraisal of (1) the
incidence of illness-related catastrophic expenditure, assessed as out-of-pocket
illness expenditure exceeding 30% of annual household income over a previous
12-month period^26^; (2) the incidence of illness-related poverty, assessed by a change in
reported household income that sees a household transition from above the
prevailing national poverty line (country specific) at baseline to below, over a
previous 12-month period; and (3) the incidence of economic hardship, defined as
perceived economic difficulties that arise as a result of chronic illness, which
alters the way people affected by illness live and manage their conditions.^27^ The economic impact of disease will be measured as a difference between
visit 1 and visit 3. Economic impact will also be compared across different CKD
stages, which will enable an appreciation of the changing costs and economic
impact associated with disease progression.

### Statistical Analysis

Continuous variables will be reported as means with standard deviations for
variables with approximately symmetric distributions and as median and
interquartile ranges (IQRs) for those with skewed distributions. Study outcomes,
including economic outcomes, will be assessed according to CKD category tested
by linear regression analysis and logistic, Cox, or Poisson regression analysis
(to estimate odds ratios, hazard ratios, and rates, respectively, with their
corresponding 95% CIs), as appropriate. Multivariable models will be constructed
adjusting for baseline variables, including country of participant,
sociodemographic information (age, sex, body mass index, ethnicity, income, and
insurance status), laboratory measurement results (estimated glomerular
filtration rate, urinary albumin measurements, hematology), and comorbid
conditions (diabetes mellitus, hypertension, atrial fibrillation, cardiac
failure). Interaction terms between CKD category and relevant variables will be
included to test for effect modification by CKD. In all time-to-event analyses,
participants will be followed from baseline until the date of the outcome,
death, or study completion. Analysis of the economic outcomes will use
multivariate logistic regression models analogous to previous work in this area^28^ Statistical analyses will be performed with SAS 7.11 (SAS Institute,
Cary, NC, USA) and Stata software (release 13; StataCorp, College Station, TX,
USA). A 2-sided *P* < .05 will be considered statistically
significant.

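### Adjusting the catastrophic-expenditure models for baseline income most plausibly conditions on the outcome's own denominator at visit 1, so the CKD-stage odds ratio should be reported both without and with income

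*Protocol article*

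**What the plan says.** In the protocol article, Statistical Analysis states that study outcomes, "including economic outcomes, will be assessed according to CKD category tested" by regression models suited to the outcome type. The multivariable models are described as "adjusting for baseline variables, including country of participant", and the covariates include "sociodemographic information (age, sex, body mass index, ethnicity, income, and" insurance status. No exception is made for the economic outcomes. A later sentence says only that these will use "multivariate logistic regression models analogous to previous work in this area", without a separate covariate list.

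Study Outcomes defines three economic outcomes:
- Catastrophic expenditure: out-of-pocket "illness expenditure exceeding 30% of annual household income over a previous" 12-month period.
- Illness-related poverty: a change in "reported household income that sees a household transition from above the" national poverty line at baseline to below it.
- Economic hardship: "perceived economic difficulties that arise as a result of chronic illness, which" changes how people live and manage their condition.

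Study Procedures describes one income measure, an item of the 56-item economic survey: "household income in the past 12 months, measured against the median" national level. Table 2 schedules the socioeconomic questionnaire at visits 1 and 3 only.

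**The concern.** Income enters one outcome and the covariate list at the same time. Study Outcomes sets out to compare economic impact across CKD stages, and the Discussion intends the results to guide resource allocation. CKD can cause catastrophic expenditure in two ways: by raising spending or by lowering income. If the model holds fixed the same income that forms the denominator, the second route drops out. The odds ratio then answers a narrower question, namely how far CKD stage raises spending at a given income. A reader who took it as the whole economic impact of CKD stage would understate the burden wherever illness has reduced earnings.

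The timing adds to this. Participants had CKD when they were enrolled in SHARP in 2003-2006, and 385 of 1136 (33.9%) were then already on renal replacement therapy (Table 3). SHARP-ER recruitment opened in August 2012, about six years after the last SHARP enrolment. Income reported at visit 1 can therefore already reflect illness.

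**Working it through.** The document gives no effect size or power for the economic outcomes, so there is no planned figure to reproduce. The check is algebra, followed by an illustrative simulation.

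**Algebra at visit 1.** Let S be out-of-pocket spending and I household income over the same 12 months. The outcome is S > 0.3 × I, or log S − log I > log 0.3. Given I, its probability is P(log S > log 0.3 + log I | CKD, I). CKD can change this only by changing S at that value of I. Any effect of CKD on I itself has been conditioned out.

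**Single-period simulation (all inputs assumed).** n = 400,000; SD of log income 0.7; SD of log spending 1.0; elasticity of spending to income 0.3; outcome prevalence 16-19%. A change of b on the log scale is a factor exp(b): exp(−0.1) = 0.90, exp(−0.3) = 0.74, exp(0.2) = 1.22.
- Advanced CKD lowers income by 10-26% and raises spending by 22%: odds ratio 1.56-1.91 without income, 1.41-1.45 with it.
- Advanced CKD lowers income by 26% and leaves spending unchanged: 1.40 without, 1.00 with.

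**Two-visit simulation (all inputs assumed).** n = 400,000 per scenario. Pre-illness log income U has SD 0.7, and lower U makes advanced CKD more likely, so confounding is built in.
- Visit-1 log income = U + b1 × CKD + noise (SD 0.3).
- Visit-3 log income = visit-1 log income + b3 × CKD + noise (SD 0.3).
- Log spending = log 0.10 + bo × CKD + noise (SD 1).

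Total means adjusted for U, which the study does not describe collecting. Adjusted means visit-1 income is in the model. Poverty is the transition among households above the line at visit 1.

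| b1, b3, bo | Catastrophic, visit 1: total → adjusted | Catastrophic, visit 3: total → adjusted | Poverty: adjusted |
|---|---|---|---|
| −0.2, −0.1, 0 | 1.39 → 0.99 | 1.61 → 1.17 | 1.82 |
| −0.4, −0.2, 0 | 1.97 → 1.02 | 2.59 → 1.40 | 3.19 |
| −0.4, −0.2, 0.3 | 3.17 → 1.67 | 4.10 → 2.25 | 3.21 |
| −0.4, 0, 0.3 | 3.17 → 1.68 | 3.00 → 1.63 | 0.99 |
| 0, −0.3, 0.3 | 1.64 → 1.69 | 2.58 → 2.70 | 5.82 |
| 0, −0.3, 0 | 1.01 → 1.01 | 1.58 → 1.61 | 5.91 |

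Reading the table:
- **Visit 1.** Where CKD lowers income only (rows 1-2), the whole effect disappears. Where it also raises spending (rows 3-4), only the spending part remains.
- **Visit 3.** Loss already present at visit 1 is removed (rows 1-4). Loss between the visits is kept (rows 5-6 show no attenuation).
- **Poverty.** Visit-1 income is the starting value of the transition. The adjusted odds ratio stays at 1.82-5.91 whenever CKD causes later income loss. It is 0.99 only in row 4, where no such loss occurs.

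**The case against.** The strongest objection is that income may be a confounder and not a consequence. Suppose people with lower prior income tend to have more advanced CKD, and CKD affects neither income nor spending. The same income gap between stages then gives the same data as the income-only case above: 1.40 without income and 1.00 with it. Here 1.40 is all confounding and 1.00 is right. The data cannot separate the two accounts, and the simulations cannot either, because they assume the answer. This stands, and it means that dropping income altogether is no cure.

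A reader might also infer more than the document supports:
- **That lost income is adjusted away for illness-related poverty as well.** It is not. That outcome is a change from a baseline position, so baseline income is a legitimate starting value and a later fall is kept.
- **That economic hardship is affected in the same way.** Its definition does not contain income.
- **That all income loss is removed.** The covariates are baseline variables, so loss after visit 1 remains in the visit-3 comparison.
- **That Table 3 proves no earlier income exists.** It also omits body mass index, ethnicity and insurance status, all listed covariates, so its silence proves nothing. The identity of covariate and denominator at visit 1 is the most plausible reading, not a stated fact: the article does not define baseline for these models, and the covariate is written as income, not household income.

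Two further objections carry less weight. The crude incidence of catastrophic expenditure by stage is untouched by covariates, which is true, but the stage comparison is to be modelled. Outcome-specific covariate sets may be left to an analysis plan not shown, but here the article itself names income and applies the list to the economic outcomes.

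**Conclusion.** The point holds for catastrophic expenditure only. With baseline income in the model, the visit-1 CKD-stage odds ratio most plausibly becomes a spending contrast at fixed income, and at visit 3 the loss present by visit 1 is taken out. That is narrower than the stated aim of comparing economic impact across stages.

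Under the assumed inputs, the visit-1 attenuation runs from slight (1.56 to 1.45, with a 10% income loss) to complete (1.97 to 1.02, with no effect on spending). Where CKD has not lowered income by visit 1, there is none. The real size is unknown.

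The conclusion rests on two readings: that baseline income is visit-1 survey income, and that CKD has lowered income by then in some households. Which model should be the main one is a trade-off between blocking a pathway and leaving socioeconomic confounding. The defect is that the income-adjusted odds ratio, given alone, could be read as the full economic impact. This is an inexpensive improvement and does not invalidate the plan.

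**What to change.** State that baseline income in these models is visit-1 survey household income, or name the earlier source if there is one.

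For catastrophic expenditure, report the CKD-stage comparison twice, keeping the other listed covariates in both models:
1. Without survey income, labelled as including the income-loss pathway and open to socioeconomic confounding.
2. With survey income, labelled as the difference in spending at fixed income.

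Do not present the income-adjusted odds ratio alone as the economic impact of CKD. This point calls for no change to the poverty or hardship models.

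The cost is a line of wording and one extra model on data already collected. The downside is residual socioeconomic confounding in the model without income, which is why the two should be read together.
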